### 2.4. Vaccination and Immunogenicity Assessment

The trial staff identified potential participants living in the 80 clusters of Asante Akim North, Ghana. Trial staff, including community health volunteers, will systematically approach each household in the area to identify households with children and adolescents that will be age-eligible at the time of vaccination. Once a household with a potential participant will be identified, the parent/LAR of the child will be given basic information about the trial and invited to attend the nearest study vaccination clinic.

After arrival at the study clinic, participants and their parents/LAR will be provided with an explanation of study objectives and invited to participate following written informed consent. Assent will be sought for participants ≥11 years of age. Once consent and assent (as appropriate) will be obtained, trial staff will screen volunteers according to the inclusion/exclusion criteria and conduct a medical examination, including measuring baseline temperature to assess for temporary exclusion criteria. Demographic information (including age and address) and participant/parent/LAR contact details will be updated during this visit. Participants or their parent/LAR meeting at least one temporary exclusion criteria after the medical assessment will be informed of the reason and asked to return in ≥48 h after resolving the condition of temporary exclusion criteria for repeat assessment and re-consenting.

Consented participants will be randomized by cluster to receive either Vi-TT or MCV-A. The randomization list by cluster will be computer-generated prior to the start of the vaccination campaign and will be provided to the staff assigned for randomization to reduce discriminatory practices or unfair assignment of vaccines. Based on the cluster randomization, the appropriate vaccine will be administered by a trained member of the study team. The site of vaccination will be recorded. If the participant’s parent/LAR consent to participation in the immunogenicity substudy, a blood sample will be collected prior to vaccination by a trained staff member. The participant will be considered enrolled in the study at the point in that any medical procedure took place (i.e., blood sample collected or vaccination administered).

A study card will be provided during the annual update census, which contains the name of the study, the participant ID, and contact details for the study team will be given to all participants/parents/LAR for use if they have any concerns or if their child is admitted to hospital at any time during the study. The study card will also contain instructions for attending the study health care facilities or sentinel sites if the participant develops a fever at any time over the follow-up period of three years.

A subset of 600 participants will be selected on a 2:1 ratio (Vi-TT vs. MCV-A) to have blood samples collected at baseline (Day (D) 0) and at D28, D365, D730 and D1095 post-vaccination to assess vaccine immunogenicity. Safety assessments will include an active safety follow-up contact on day 7 to monitor adverse events following immunization in participants in the safety substudy (*n* = 3000, 1:1 assignment to intervention and control group) using study diary cards, and 3 years of passive hospital-level febrile and severe adverse event (SAE) surveillance. An independent Safety Monitoring Committee (SMC) was established to assess safety results and to correspond with the Data Safety Monitoring Board (DSMB). Randomization lists for these subsets will be generated prior to the vaccination campaign by an independent statistician who is not part of the study. The selection of these participants were age-stratified (<5 years vs ≥5 years of age, with an allocation ratio of 1:1) (Figure 1). Participants who will be enrolled in the immunogenicity substudy will receive additional face-to-face follow-up visits at the Agogo healthcare facility. At these additional visits, blood samples will be collected along with information relating to fever episodes or SAEs since the previous contact.

### 2.5. Trial Outcomes

The primary outcome of interest is the total protection of single-dose Vi-TT vaccination, measured as the incidence of blood-culture-confirmed typhoid fever in vaccinated children and adolescents, comparing intervention with the control clusters. Secondary outcomes include the occurrence of adverse events reported from participants receiving Vi-TT compared with MCV-A through active safety follow-up in a subset (safety subgroup) within the first 7 days post-vaccination and passive safety follow-up of serious adverse events within 6 months of vaccination determined by self-reporting at follow-up contact. The incidence of blood-culture-confirmed symptomatic TF, clinical TF (cases with fever persisting for >72 h), and severe TF, defined as blood-culture-confirmed TF with any one systemic complication of TF detected at presentation, will be assessed in all residents (overall protection), comparing intervention clusters with control clusters as well as in vaccinated individuals (total protection) and in unvaccinated individuals (indirect protection) [23]. The short-term (D28) and long-term (D365, D730, and D1095) seroconversion rates and antibody response against *S.* Typhi (anti-Vi IgM and IgG) and invasive non-typhoidal Salmonella after Vi-TT administration will be determined at defined timepoints.

Exploratory outcome measures include the assessment of incidence of clinically diagnosed intestinal perforations that are associated with *S*. Typhi, incidence of acute abdominal surgery and surgical procedure on intestinal perforations, and all-cause hospitalization rates in all residents and in vaccinees of the intervention cluster compared with the control clusters. The analysis of mortality rates assessed through verbal autopsy in the study area differentiates between all-cause mortality, mortality with fever, and mortality with fever and abdominal pain between the intervention clusters compared with the control vaccine clusters. In addition, the prevalence of antimicrobial-resistant *S.* Typhi pre- and post-vaccination will be compared between the intervention and control clusters, and the corresponding antimicrobial prescription patterns were observed in participating health care facilities that are part of the existing surveillance system.

### 2.6. Sample Size/Statistical Methods

The sample size was calculated by assuming an expected cumulative incidence rate of typhoid fever in control clusters over 3 years of 36 cases per 10,000 person-years in a catchment population of 21,213 i.e., 45,961.5 person-years of risk. Based on a preliminary analysis of survey data from the target population, we assumed that 50% of febrile illness cases seek healthcare at Agogo Presbyterian Hospital [24]. A total of 80 clusters were formed in 15 villages considering the natural settlement of the population and administrative borders. The current average number of children and adolescents aged 9 months to less than 16 years per village was 287 based on the population census in 2019 (see Table 1). We estimated the vaccine coverage at 65% and a total effectiveness of 80% with a coefficient of variation of 0.5 for a one-sided test of significance at an alpha of 0.05.

Following Hayes and Moulton, a total sample size of 13,200 person-years, which was obtained by sampling 80 clusters (40 in each arm) with an average cluster size ranging from 145 to 180, achieved >80% power to detect a total effectiveness of 80% between the intervention event rate 0.0007 and the control event rate 0.0036 [25]. The between-cluster coefficient of variation in the control and treatment groups was assumed as 0.500. A two-sided t-test of the event-rate difference was used with a significance level of 5%. The total sample sizes ranging from 11,600 to 14,400 adjusted for 15% drop-out rate were within target eligible population size considering 65% vaccine coverage.

For the immunogenicity substudy, a total of 600 children and adolescents will be enrolled, stratified by age (<5 years and ≥5 years). Each age stratum was randomized 2:1 to receive the intervention (*n* = 200) or control vaccine (*n* = 100) with an assumption of a 90% reference seroconversion rate, −10% of non-inferiority margin, and 25% drop-out rate.

For the safety monitoring substudy, a total of 3000 children and adolescents with a 1:1 ratio of each arm will be enrolled according to the “rule of three” to detect at least one event with 1500 participants in each arm. The upper limit of 95% CI of the incidence rate yielded 0.2% in each arm [26].

The primary outcome measure is blood-culture-positive TF detected during passive surveillance (see Section 3) at the study sites in vaccinees of the inner clusters demarcated geographically at baseline. To evaluate the heterogeneity of Vi-TT vaccine protection among the different subgroups, we will evaluate the interaction terms between the vaccination and subgroup variables in the models. *p*-values for the analyses will be calculated as two-tailed. Subgroup analyses will include different age stratifications (<5 years and ≥5 years; <2 years and ≥2 years) and gender (male *versus* female). The subgroup analysis was not powered to evaluate the primary outcome, and any observed patterns were interpreted cautiously, owing to the large study population and increased chance of type I error.

For safety assessment in the subset for active follow-up, solicited and unsolicited adverse events (AEs) at day 7 post-vaccination will be assessed. The frequency and proportion of participants who experience solicited AE and unsolicited AE post-vaccination will be presented with the 95% CI. Additionally, the number of participants and number of occurrences of AEs by vaccine arm for each age strata as well as overall ages were assessed. The occurrence of any SAE within 6 months follow-up post-dose will be also summarized and listed.

An immunogenicity analysis will be presented as the geometric mean titre (GMT) with 95% CI at baseline (D 0), D 28, D 365 D 730, and D 1095, and as a proportion of four-fold increase from baseline (seroconversion rate) with 95% CI at D 28, D 365, D 730, and D 1095.

Data defined by the study protocol will be captured in a clinical study database using REDCap [27]. All clinical and laboratory data were entered from paper forms into the electronic data capture (EDC) system. Data will be entered using tablets, laptops, or computers into a web-based version of the electronic case report forms (eCRFs). Edit checks programmed within the eCRFs will validate the data at the time of data entry. Performance qualification of the eCRFs will be performed, in particular on the edit checks. Data entry and subsequent data handling will be performed by trained study staff under the supervision of the site investigators.

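### The sample-size text specifies both a one-sided 5% test and a two-sided 5% test for the primary total-effectiveness comparison

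*Protocol article*

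**What the plan says.** Section 2.5 of the protocol article names total protection of single-dose Vi-TT against blood-culture-confirmed typhoid fever as the primary outcome. Section 2.6 then describes the test for that comparison in three places.

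- The first paragraph lists 65% coverage, 80% total effectiveness and a coefficient of variation of 0.5, "for a one-sided test of significance at an alpha of 0.05".
- The second paragraph reports that the design "achieved >80% power to detect a total effectiveness of 80" per cent, and adds: "A two-sided t-test of the event-rate difference was used with a significance level of 5" per cent.
- Later, among the sentences on subgroups and interaction terms, the section says that p "values for the analyses will be calculated as two-tailed". It gives no significance level there.

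Nothing says that one of these statements replaces another.

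**The concern.** The first two statements concern the same quantity, with the same effectiveness and the same coefficient of variation. They cannot belong to different endpoints, because the immunogenicity and safety subset calculations follow in paragraphs of their own.

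A one-sided test at 5% and a two-sided test at 5% set different thresholds for claiming that the vaccine works. A result with a one-sided p-value between 0.025 and 0.05 passes the first and fails the second. While both stand in print, the looser threshold could be adopted after the data are seen and defended from the published text. The sidedness of a primary comparison should be unambiguous before unblinding.

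**Working it through.** **Inputs, all from Section 2.6.** Rates: "between the intervention event rate 0.0007 and the control event rate 0.0036". Clustering: "The between-cluster coefficient of variation in the control and treatment groups was assumed as 0.500". Size: "80 clusters (40 in each arm) with an average cluster size ranging from 145 to 180", with "a total sample size of 13,200 person-years" in total.

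**Reproducing the plan's totals.** 145 × 80 = 11,600; 165 × 80 = 13,200; 180 × 80 = 14,400. All three match the article, so the cluster size is read as person-years per cluster, with 165 as the central value.

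**False-positive rate in the favourable direction.**
- One-sided 5%: 0.05, critical z = 1.645.
- Two-sided 5%: 0.05/2 = 0.025, critical z = 1.960.

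**Power.** The Hayes–Moulton formula for unmatched clusters is

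c = 1 + (z_α + z_β)² · V, where V = [(r0 + r1)/y + k²(r0² + r1²)] / (r0 − r1)².

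Solved for power at c = 40 per arm, this gives power = Φ(√(39/V) − z_α).

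With r0 = 0.0036, r1 = 0.0007, k = 0.5 and y = 165:
- (r0 + r1)/y = 0.0043/165 = 2.606 × 10⁻⁵
- k²(r0² + r1²) = 0.25 × 1.345 × 10⁻⁵ = 3.363 × 10⁻⁶
- (r0 − r1)² = 0.0029² = 8.41 × 10⁻⁶
- V = 2.942 × 10⁻⁵ / 8.41 × 10⁻⁶ = 3.499, and √(39/3.499) = 3.339
- Two-sided: Φ(3.339 − 1.960) = 91.6%
- One-sided: Φ(3.339 − 1.645) = 95.5%

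| Person-years per cluster | Two-sided 5% | One-sided 5% | Difference (points) |
|---|---|---|---|
| 145 | 88.3% | 93.4% | 5.1 |
| 165 | 91.6% | 95.5% | 3.9 |
| 180 | 93.4% | 96.6% | 3.2 |

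The article's power of more than 80% is therefore met under both readings. It is only a lower bound, so it cannot show which sidedness was used.

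**Sensitivity at 165 per cluster.** A noncentral t version with 78 degrees of freedom gives 91.6% two-sided and 95.6% one-sided. Setting r1 to 0.00072, which is exactly 80% effectiveness, gives 91.1% and 95.2%. For 80% power the formula needs 29 clusters per arm two-sided and 23 one-sided, against 40 planned.

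**How often the threshold would decide the verdict.** The last column of the table is the chance that the one-sided p-value falls between 0.025 and 0.05 at the printed 80% effectiveness: about 3–5%. With no effect, that chance is 0.05 − 0.025 = 2.5%. If true effectiveness were 60% (an assumption for illustration, not in the article; r1 = 0.4 × 0.0036 = 0.00144), power at 165 per cluster would be about 63% two-sided and 74% one-sided. The threshold would then decide about 11% of trials.

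**The case against.** The strongest reply is that neither alpha statement is a decision rule. Both sit in the sample-size text: the first closes a list of assumptions, and the second reports in the past tense how power was calculated. The rule for the primary analysis would normally stand in the full protocol or the analysis plan, which are not shown, and its absence from an article is no fault. The only sentence that looks forward to the analysis says that p-values are two-tailed, so the one-sided phrase is most plausibly a leftover. Power is adequate under either reading.

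Much of this stands. A reader might infer that the trial's primary decision rule is itself contradictory, or that its type I error is really 5%. The article does not support that, because it gives no separate rule for the primary analysis and a sample-size assumption does not by itself fix the error rate. A reader might also infer that a 90% confidence interval is planned. None is mentioned, and the intervals the article plans for safety and immunogenicity are 95%. Nor does the conflict make the trial too small: even with the 15% drop-out taken off the smallest cluster size (145 × 0.85 ≈ 123 person-years), the same formula gives about 83% power two-sided.

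The reply does not remove the discrepancy. This is not detail left to another document: the article states sidedness and alpha twice, incompatibly, in adjacent paragraphs. The two-tailed sentence indicates intent, but it stands among the subgroup text, gives no alpha and does not withdraw the one-sided phrase.

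**Conclusion.** Wrong as written, of moderate severity. For the primary total-effectiveness comparison, the sample-size text gives two incompatible test specifications, and these are the article's only alpha statements for that outcome. If carried into the analysis, they imply a 5% or a 2.5% chance of a false claim of benefit. The power calculation and the later p-value sentence both point to two-sided testing, so the one-sided phrase is the likely error.

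The sample size and the power claim are unaffected. This conclusion takes the printed rates, coefficient of variation and cluster sizes as given, and reads 145 to 180 as person-years per cluster at those rates. Whether those inputs are themselves sound is a separate matter.

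**What to change.** In the first paragraph of Section 2.6, delete "for a one-sided test of significance at an alpha of 0.05". State once, for the primary comparison, that the test is two-sided at 5% and that total effectiveness is reported with a 95% confidence interval. Carry the same sentence into the analysis plan before unblinding, if it is not already there.

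The cost is one sentence. Against a one-sided 5% test, the two-sided test gives up about 3 to 5 percentage points of power on the printed inputs. It still leaves 88% or more and needs no change to the number of clusters or participants.

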### 2.2. Cluster Randomization and Method of Blinding

The TyVEGHA study population was recruited from a geographically defined catchment area in the Asante Akim District of Ghana (see Figure 1, TyVEGHA catchment area). The baseline map of the area was developed in partnership with the Statistical Service office in Agogo, Ghana. Additional data from a baseline census were used to inform details on the map and to confirm the catchment area boundaries for the trial. The census population data were merged with the Geographic Information System mapping (GIS,) data for cluster formation (QGIS.org, 2021. QGIS Geographic Information System. QGIS Association.). The study area was divided into 80 clusters. Each cluster consisted of a total population of 400–600 inhabitants at average, with an estimated proportion of 40% in the eligible age group for TyVEGHA. The entire age-eligible cluster population was eligible for vaccination and analized under primary analysis. In addition, a buffer region formed at the border of each cluster, was drawn to insulate adjacent clusters, minimizing cross-cluster transmission [21] if necessary. The age-eligible individuals residing in the inner region served as the population under exploratory analysis.

GIS mapping tools were used for identification of all geographical characteristics and demarcation of clusters [22]. Randomization lists allocated each cluster to receive either Vi-TT or the control vaccine MCV-A in equal numbers (40 clusters in each arm), based on population size, using stratified block randomization. Stratification was by clusters, the distance to the closest healthcare facility (above the median versus at or below the median), and the percentage of children and adolescents aged 9 months to <16 years age (above the median versus at or below the median).

Once participants will be enrolled in the study, they will be vaccinated with either the trial or the control vaccine according to the residential cluster in which they live. Census updates were conducted annually to identify birth and mortality rates as well as in- and out-migration in the defined clusters. The census was designed to capture (1) socioeconomic information of the households, including profession, household income, and level of education and (2) healthcare-seeking behavior and to access to water, sanitation, and hygiene (WaSH) infrastructure. Household verbal consent for the census was provided by the head or a key informant of the household.

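### Sections 2.2 and 2.6 name different primary analysis populations (whole cluster versus inner-cluster vaccinees), and no power is stated for the inner-cluster version

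*Protocol article*

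**What the plan says.** Section 2.2 of the protocol article deals with the whole cluster first: "The entire age-eligible cluster population was eligible for vaccination and analized under primary analysis". It then describes a border zone: "a buffer region formed at the border of each cluster, was drawn to insulate adjacent clusters, minimizing cross-cluster transmission [21] if necessary". The area inside that zone has a lesser role: "The age-eligible individuals residing in the inner region served as the population under exploratory analysis".

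Section 2.6, after the sample-size paragraphs, defines the primary outcome measure as blood-culture-positive typhoid fever found by passive surveillance "in vaccinees of the inner clusters demarcated geographically at baseline".

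Section 2.5 describes the primary outcome, total protection, as "measured as the incidence of blood-culture-confirmed typhoid fever in vaccinated children and adolescents, comparing intervention with the control clusters". It mentions no inner zone.

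The power statement in Section 2.6 refers to "a total sample size of 13,200 person-years", "obtained by sampling 80 clusters (40 in each arm) with an average cluster size ranging from 145 to 180", and to a contrast "between the intervention event rate 0.0007 and the control event rate 0.0036". It mentions neither a buffer nor an inner region.

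**The concern.** The same inner region is exploratory in Section 2.2 and primary in Section 2.6, and nothing in the article says which statement prevails. This is not detail left to an analysis plan. The article fixes the population for its main claim twice, in incompatible ways, and any analysis plan can agree with only one of them.

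The choice has consequences. Restricting to the inner zone removes cases and person-time. It also changes what is estimated: border residents are the people most exposed to transmission from a neighbouring cluster in the other arm, which is the reason Section 2.2 gives for drawing a buffer. The two analyses can therefore differ in both the estimate and its precision. A reader also needs to know which of them the stated power belongs to.

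**Working it through.** **Inputs.** From Section 2.6: 40 clusters per arm (c = 40); control rate λ0 = 0.0036; intervention rate λ1 = 0.0007; between-cluster coefficient of variation k = 0.5; 13,200 person-years in total; 145 to 180 per cluster; coverage 65%; drop-out 15%; 45,961.5 person-years in 21,213 people. From Section 5 and Table 1: 22,973 age-eligible residents. The test is taken as two-sided at 5%, as in the power paragraph. The share of vaccinees living in the inner region is not given; 75%, 60%, 50% and 40% are assumptions.

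**Step 1: reproduce the stated power.** The Hayes–Moulton formula for unmatched rates, solved for power with y units of exposure per cluster, is

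power = Φ( √[ (c − 1)(λ0 − λ1)² / V ] − 1.96 ), with V = (λ0 + λ1)/y + k²(λ0² + λ1²).

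At y = 165 (13,200/80):
- V = 0.0043/165 + 0.25 × (0.0036² + 0.0007²) = 2.606×10⁻⁵ + 0.336×10⁻⁵ = 2.942×10⁻⁵
- √[39 × 0.0029² / V] = 3.34
- power = Φ(1.38) = 91.6%

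At y = 145 it is 88.3%, and at y = 180 it is 93.4%. All agree with the stated power above 80%.

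**Step 2: which population do these sizes describe?**
- 22,973/80 = 287 eligible per cluster. (Section 2.6 gives 287 as a per-village average, but the division by 80 shows that it is per cluster.)
- 287 × 0.65 = 187 vaccinees per cluster.
- 187 × 0.85 = 159 after drop-out.

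The figure enters the stated range of 145 to 180 only after the drop-out step. No further reduction is needed, so the sizes fit vaccinees of whole clusters, with nothing taken off for a buffer. This is inferred from the arithmetic; the article does not say so.

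**Step 3: power if only the inner region counts.** The result depends on what 165 measures. Reading A takes it as person-years per cluster, following the article's 13,200 person-years. Reading B takes it as persons, each followed for 45,961.5/21,213 = 2.17 years, which gives 165 × 2.1667 = 357.5 person-years per cluster.

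| Assumed inner share | A: y | A: power | B: y | B: power |
|---|---|---|---|---|
| 75% | 123.8 | 83% | 268.1 | 98% |
| 60% | 99.0 | 75% | 214.5 | 96% |
| 50% | 82.5 | 68% | 178.8 | 93% |
| 40% | 66.0 | 59% | 143.0 | 88% |

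Under A, 80% power needs y of about 112, an inner share of 112/165 = 68%. Under B, every share in the table stays above 80%.

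**Step 4: expected cases in whole clusters.** Under A: 40 × 165 × (0.0036 + 0.0007) = 28. Under B: 40 × 357.5 × 0.0043 = 61.

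**The case against.** The strongest reply concerns the consequences, since the conflict in wording is plain.

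- **Lost power is not established.** Follow-up is three years, and Section 2.6 calls its rate cumulative over 3 years yet expresses it per person-year. Under reading B an inner-cluster analysis keeps 88% power even at a 40% share. The buffer is drawn only if needed and its width is not given, so the true share could be high. The calculation also holds the effect at 80% in both zones; if spill-over dilutes the whole-cluster effect, the cost of restricting to the inner zone is overstated. All of this stands. A reader might infer that an inner-cluster analysis would be underpowered; the article supports only that its power is not stated.
- **Choice after seeing the data is not shown.** A reader might infer that the primary result could be picked once results are known. The analysis plan is not available and may settle the matter, the trial is observer-blinded, and Section 2.6 fixes the inner boundary at baseline. What is open in this text is which population is primary. That is a risk, not a demonstrated event.
- **Section 2.5 is not a third definition.** Its wording is general and does not rule out a geographic restriction. This stands.
- **Unvaccinated residents.** Read literally, Section 2.2 would put unvaccinated eligible residents into the primary analysis. The Abstract makes total protection primary, Section 2.5 measures it in the vaccinated and places the unvaccinated and all residents under secondary outcomes, and Section 2.6 also says vaccinees. The wording of Section 2.2 is loose and worth tightening, but an analysis that includes the unvaccinated is not what the article intends.

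None of these points removes the conflict between Sections 2.2 and 2.6.

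**Conclusion.** The contradiction is real and concerns the trial's main claim: the inner region is exploratory in Section 2.2 and primary in Section 2.6. The sample size appears to have been derived for whole-cluster vaccinees, for whom the stated power is reproduced (91.6% at 165 per cluster). Power for an inner-cluster primary analysis is not stated. Across the assumed shares of 75% to 40%, it runs from 83% down to 59% on the person-years reading and from 98% down to 88% on the persons reading. The documents do not settle which reading is right or what the share is. The need for correction rests on the conflicting definitions and does not depend on either power figure.

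**What to change.** Before unblinding, name one primary population and use it in Sections 2.2, 2.5 and 2.6. Vaccinees resident anywhere in the cluster at vaccination, compared between Vi-TT and MCV-A clusters, fit Section 2.5, the whole-cluster scope of Section 2.2 and the sample size.

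- Section 2.2: say that the primary analysis covers vaccinees of the entire cluster.
- Section 2.5: add that vaccinees from the whole cluster are meant.
- Section 2.6: make inner-cluster vaccinees the pre-specified exploratory analysis.

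This choice is not compelled. If the sponsor keeps the inner region as primary, Section 2.2 must be corrected instead, the share of vaccinees in the inner region stated, and the power restated for it, making clear whether the cluster sizes are persons or person-years.

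The first option costs a few sentences and no new data. The second also needs the inner share, to be obtained from the census and mapping data, and one power calculation.
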